### Randomisation method and blinding

Forty participants who meet the inclusion criteria will be randomly assigned to either the intervention or control group. An independent statistician will generate the stratified randomisation sequence using Stata 16. Stratified randomisation with a 1:1 allocation ratio will be used to ensure balance across key characteristics, including age, sex and SCI severity as classified by the American Spinal Injury Association (ASIA). These variables were selected a priori because they are clinically important prognostic factors known to influence recovery and functional outcomes after SCI and imbalance across groups could bias treatment effect estimates. We acknowledge that the number of potential strata is relatively large compared with the target sample size (n=40), which may result in sparse strata. To address this, a restricted randomisation approach will be used (eg, permuted block randomisation). In addition, baseline characteristics will be carefully assessed, and any residual imbalance in key variables (particularly SCI severity) will be adjusted for in the primary analysis. This will be done in collaboration with the statistician on the team. This approach balances the need to control for important prognostic factors with the practical constraints of a small sample. Randomisation will occur after the initial assessment (T1). Neurological level and injury severity will be determined using the ISNCSCI,^30

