31^ with impairment categorised according to the ASIA Impairment Scale, ranging from A (complete injury with no sensory or motor function preserved in sacral segments S4–S5) to E (normal function). Age will be categorised into three groups: 16–34 years, 35–49 years and 50+ years. Sex will be categorised into two groups: male and female. These variables were selected for stratification due to their potential influence on outcomes and to minimise confounding effects.^32–35^ To maintain balance in recruitment over time, permuted block randomisation will be employed with block sizes of 4 or 6. This approach will ensure equal distribution of participants between the intervention and control groups within each block, thereby reducing the risk of imbalance as the study progresses. The permutation of blocks will randomise the order of allocation, further enhancing the reliability and reproducibility of the randomisation process. A total of 40 participants will be included in the randomisation process to account for potential dropouts before the completion of the study (see section Power calculation). Consequently, 24 separate randomisation lists or *strata*, each containing 40 participants, will be generated based on the stratification variables. All study personnel involved in the clinical assessments will remain blinded to the group allocation. Participants will also remain blinded to their assigned group throughout the study. The interventionist will not be blind to the group allocation due to the immediate effect of tSCS.

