### Statistical analysis

The Shapiro-Wilk test will be used to assess the distribution of continuous variables for both demographic and outcome measures. Normally distributed continuous data will be summarised as mean with SD, while non-normally distributed data will be presented as median with IQR. Categorical variables will be reported as frequencies and percentages. Specific injury-related characteristics (eg, level and severity of injury) will be considered for exploratory subgroup analyses. To evaluate changes over time and differences between groups, a linear mixed-effects model will be fitted with fixed effects for group (ABT+tSCS and ABT+sham), time (pre, post and 1-month follow-up) and the group×time interaction and a random effect for participant to account for within-subject correlations across repeated measurements. The primary effect of interest will be the group×time interaction, which will be used to determine whether changes over time differ between groups. Where a significant group×time interaction is observed, estimated marginal means will be compared using post hoc pairwise contrasts with appropriate adjustment for multiple comparisons. Missing data will be handled using an intention-to-treat approach, with all available observations included in the mixed-effects model. If warranted, sensitivity analyses using multiple imputation may also be conducted to assess the robustness of the findings. The threshold for statistical significance will be set at p<0.05 for all analyses.

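### Adjustment of the primary analysis depends on observed baseline imbalance, and the stated model includes neither the stratification factors nor baseline UEMS as a covariate; the set should be fixed in advance

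*Protocol article*

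**What the plan says.** Under Randomisation method and blinding, the protocol article stratifies by age (three groups), sex (two) and AIS grade. It describes these as clinically important prognostic factors chosen a priori, and adds: "These variables were selected for stratification due to their potential influence on outcomes and to minimise confounding effects". It concedes that strata may be sparse at n=40. Baseline characteristics will then be examined, and "any residual imbalance in key variables (particularly SCI severity) will be adjusted for in the primary analysis". On how, it says only: "This will be done in collaboration with the statistician on the team".

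Under Statistical analysis, the model has "fixed effects for group (ABT+tSCS and ABT+sham), time (pre, post and 1-month follow-up) and the group×time interaction", together with "a random effect for participant to account for within-subject correlations across repeated measurements". The test is also fixed there: "The primary effect of interest will be the group×time interaction". T1 is one of the three levels of time, so baseline UEMS enters as a response. No stratification factor and no baseline covariate is listed.

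**The concern.** Three linked matters.

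1. **Trigger.** The rule makes the content of the primary model depend on what the baseline table shows. This is a rule the article states, not a detail it leaves out. A factor judged prognostic in advance belongs in the model whether or not the arms happen to differ on it.

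2. **Form.** In a model where T1 is a response and the effect of interest is an interaction with time, a covariate that is constant over time does not act as it would in an ordinary regression. Entered as a main effect, it moves all three visits by the same amount and drops out of the treatment contrast. A team could then report a severity-adjusted result that is practically the unadjusted one.

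3. **Precision.** With separate T1 means per arm, the group×time contrast is a comparison of change scores. With 40 participants, the gain from conditioning on baseline UEMS is worth having.

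**Working it through.** **Design figure.** Strata: 3 age groups × 2 sexes × 4 AIS grades = 24, as the article states. 40/24 = 1.67 participants per stratum against blocks of 4 or 6, so most blocks will not fill and chance imbalance in AIS is possible despite stratification.

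**How a main effect cancels.** With complete data, the T2 interaction estimate is

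(mean T2 − mean T1) in ABT+tSCS − (mean T2 − mean T1) in ABT+sham.

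A term β×AIS is the same at T1 and T2 for each person, so it subtracts out. A term that differs by visit does not.

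**Numerical check.** None of the following inputs is in the article: 20 per arm, SD 10, correlation 0.8, true effect 0, AIS A 12 in the sham arm and 8 in the active arm, mean gain 4 points in AIS A and 8 in the others. T2 group×time in one simulated complete dataset:

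| Model | Estimate |
|---|---|
| As stated | 2.026 |
| + severity | 2.026 |
| + severity + baseline UEMS, as main effects | 2.026 |
| + severity×time | 0.782 |

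The expected conditional error of the stated model here is (12 − 8)/20 × (8 − 4) = 0.8 points. Averages over 400 simulated trials, with dropout meaning 6 of 40 (15%) lost after T1:

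| Correlation | Data | As stated | + severity | + severity×time |
|---|---|---|---|---|
| 0.8 | complete | 0.840 | 0.840 | 0.024 |
| 0.8 | dropout | 0.629 | 0.629 | −0.196 |
| 0.5 | complete | 0.734 | 0.734 | −0.111 |
| 0.5 | dropout | 0.741 | 0.728 | −0.033 |

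The averages carry simulation error (about 2.156/√400 = 0.11 in the second row). The gap between the stated and the severity×time model is steadier: 0.816, 0.825, 0.845 and 0.774, all near 0.8. With dropout the main effect does move single estimates (mean absolute shift 0.13 at correlation 0.8 and 0.36 at 0.5, against standard errors of 2.16 and 3.38), but not their average.

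Conditioning on baseline works only if severity is in the model too. For 12 vs 8, T2 regressed on group, baseline and severity averaged −0.03; with baseline but without severity it averaged 0.93.

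**Likely imbalance.** Simulating 24 strata with blocks of 4 or 6 and n=40 (assumed: AIS grades in equal quarters or 35/12/13/40%; sex 75/25; equal age groups):

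- mean absolute difference in AIS A counts: about 1.8 to 1.9 patients;
- difference of 3 or more: 27–30% of trials;
- 4 or more: 13–14%;
- 6 or more: about 2% (7–9% if the split is A/B vs C/D).

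Conditional error = difference/20 × difference in gain:

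- 2 patients: 2/20 × 4 = 0.4, or 2/20 × 5 = 0.5 points;
- 4 patients: 4/20 × 4 = 0.8 points;
- 6 patients: 6/20 × 5 = 1.5 points.

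**Precision.** With equal variance at both visits and correlation ρ, the change contrast has variance proportional to 2(1 − ρ) and the baseline-adjusted contrast to 1 − ρ². The ratio is (1 − ρ²)/[2(1 − ρ)] = (1 + ρ)/2: 0.75 at ρ=0.5, 0.85 at 0.7, 0.90 at 0.8 and 0.95 at 0.9. The saving is 25%, 15%, 10% and 5%. The article does not give ρ, and the formula ignores the degrees of freedom spent.

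**The case against.** The strongest reply is that the two sections fit together: Statistical analysis gives the core model, and the randomisation section adds adjustment to it, with a statistician in charge. The functional form is what a condensed article leaves to the analysis plan, and a severity×time term would correct the imbalance. This stands. A reader might infer that the plan's own remedy fails and that the primary estimate will carry the bias while being called adjusted. The documents do not support that, because they never say that severity would enter as a main effect.

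It is also fair that the unadjusted contrast is unbiased over repeated randomisation. A chance imbalance gives error conditional on the allocation obtained, and nothing here shows an inflated type I error. Nor is baseline UEMS ignored: it is in the model as the T1 response, and such models are standard and valid. Only the extra precision is lost, and that is small if ρ is high. Finally, an example such as 13 vs 7 with a 5-point difference in gain (1.5 points) would be a poor guide to the usual size, since an AIS A difference of 6 or more arises in about 2% of simulated trials.

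The reply does not remove the trigger. Making adjustment conditional on observed imbalance is stated outright, and a later plan that fixed the covariates would have to depart from it.

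**Conclusion.** The point holds as a cheap improvement that should be made, not as a fatal flaw. Adjustment is tied to imbalance seen in the data, and the only model given contains none of the factors the article itself calls prognostic. The cancellation is certain as algebra for complete data and holds on average with dropout, but it is a caution about how to implement adjustment. The typical size is modest: about 0.4 to 0.5 UEMS points for a 2-patient AIS A imbalance, against a standard error near 2 in the illustration. That rests on assumed case mixes, an assumed 4- to 5-point difference in gain and an assumed SD of 10. The precision forgone is about 5% to 25% of variance for ρ from 0.9 to 0.5. At the high end of ρ, the case for change rests mainly on fixing the covariates in advance.

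**What to change.** Replace the imbalance sentence under Randomisation method and blinding with a covariate set named under Statistical analysis and used whatever the observed balance. For example:

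> UEMS at T2 and T3 will be the responses, with fixed effects for group, visit, group×visit, baseline UEMS, baseline UEMS×visit, AIS (collapsed, eg A/B vs C/D), AIS×visit, age group and sex, and a random participant effect. All covariates are included regardless of baseline balance.

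A model that keeps T1 as a response, with a common baseline mean for the two arms and AIS×visit, is an equivalent option. If the present model is kept instead, state that any severity term is crossed with time.

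All covariates are already collected. The cost is wording and, in the example, seven further coefficients (2 for baseline UEMS, 2 for AIS, 2 for age group, 1 for sex), which is tolerable but not nothing at n=40; this is why AIS is collapsed. The change should be made before any baseline data are examined.

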### Assessments

#### Outcome measures

Participants will be assessed before the intervention (T1), post-intervention (T2) and at 1-month follow-up (T3) (see table 2). All clinical assessments will be administered by a trained occupational or physical therapist blinded to the group assignment. The same assessor will remain across all assessment time points.

**Table 2 T2:** Primary and secondary outcome measures and assessment timepoints

Assessment	Timepoint			
	T1	Intervention	T2	T3
Primary outcome measures				
Upper-limb motor score of the ISNCSCI	x		x	x
Secondary clinical measures				
Prehension subtest of the GRASSP	x		x	x
Tetraplegic Upper Limb Activity Questionnaire	x		x	x
Grip and pinch strength	x		x	x
Upper-limb sensory score of the ISNCSCI	x		x	x
Monofilaments test	x		x	x
Proprioception subtest of the Fugl-Meyer Assessment	x		x	x
Finger-to-nose test	x		x	x
Neurophysiological measures (secondary)				
Transspinal-evoked potentials	x		x	x
Motor-evoked potentials	x		x	x
Somatosensory-evoked potentials	x		x	x

GRASSP, Graded Redefined Assessment of Strength, Sensibility and Prehension; ISNCSCI, International Standards for Neurological Classification of Spinal Cord Injury.

The clinical assessment battery will take approximately 2 hours to complete. All assessment results will be entered into the secure REDCap platform (Vanderbilt University, Nashville, TN), which complies with institutional and provincial data governance and confidentiality standards. Data entry will be performed by authorised personnel only, using coded identifiers to ensure participant confidentiality. All REDCap entries will be verified by another team member before locking the scores.

#### Primary measures

##### Primary outcome measure

*Upper limb strength:* The UEMS of the ISNCSCI aims to manually assess muscle strength at each metameric level using a scoring system from 0 to 5. Specific muscle actions are tested to represent each level: elbow flexion for C5, wrist extension for C6, elbow extension for C7, middle finger flexion for C8 and fifth finger abduction for T1. The scores range from 0 (no visible or palpable muscle contraction) to 5 (normal active movement, full range of motion against gravity and full resistance). The UEMS demonstrates excellent inter-rater reliability (intraclass correlation coefficient (ICC): 0.99) and a moderate to good validity (Spearman coefficient r=0.91).^36–38^

##### Secondary clinical assessments

*Upper limb activity limitation:* The Prehension subtest of the Graded Redefined Assessment of Strength, Sensibility and Prehension (GRASSP), V.2,^39^ is a standardised clinical outcome measure used to evaluate hand function through the assessment of grasp patterns and object manipulation abilities in individuals with cervical SCI. This subtest includes both qualitative and quantitative components. The qualitative component, called Prehension Ability, assesses the ability to perform three grasp patterns (eg, cylindrical, lateral pinch and tip pinch) based on the presence and quality of movement. Each hand is tested separately and scored from 0 to 4. A score of 4 indicates normal voluntary control of the wrist and digits when generating the respective grasp.

The quantitative component, Prehension Performance, involves functional tasks in which participants are asked to grasp, manipulate and release objects of varying shapes and sizes. Each hand is tested separately. The items are rated on a scale from 0 to 5. A maximum score of 5 indicates that the participant successfully solved the task using the expected grasp pattern. The GRASSP prehension has excellent test–retest reliability (ICC=0.93–0.98) and excellent inter-rater reliability (ICC=0.95–0.96).^39^

*Self-perceived upper limb function:* The Tetraplegic Upper Limb Activity Questionnaire (TUAQ) is a self-reported measure of upper limb function and satisfaction for individuals with tetraplegia. The TUAQ comprises 10 items, rated on a 5-point Likert scale ranging from 1 (not able to perform/not satisfied with the performance at all) to 5 (able to perform extremely well/extremely satisfied). Responses to each item are summed to obtain a raw score for each scale. This raw score is converted using a conversion table. The total score is between 0 and 100 for each scale, with a higher score indicating a higher performance or satisfaction. The TUAQ has good test-retest reliability for performance (ICC=0.89) and for satisfaction (ICC=0.88) and a high construct validity for TUAQ performance and satisfaction scales (rho: 0.19–0.52).^40^

*Grip and pinch strength:* The grip strength is evaluated with a JAMAR dynamometer, whereas the lateral, 2- and 3-point pinches are evaluated with a JAMAR pinch gauge. The participant sits with the elbow at 90 degrees, forearm neutral and wrist slightly extended and is asked to squeeze the device as hard as they can. The participant performs three trials for each pinch/grip type, and the average is recorded for each hand. There is an excellent inter-rater (ICC: 0.79–0.92) and excellent intra-rater reliability (ICC: 0.79–0.96).^41
42^

*Sensation:* Sensory function will be assessed using the ISNCSCI.^43^ Light touch and pinprick sensation will be examined bilaterally for dermatomes C4 to T1 at standardised sensory points on the upper limbs. Light touch will be tested using a cotton swab, and pinprick sensation will be assessed using a toothpick. Each dermatome and sensory modality is scored as 0 (absent), 1 (impaired or altered) or 2 (normal), based on comparison with sensation at an intact reference area. The sensory score of the ISNCSCI for the dermatomes from C4 to T1 detects the presence, alteration or loss of sensory function of spinal origin and assesses the participant’s ability to discriminate between light touch and sharp stimuli. The sensory function demonstrates excellent inter-rater reliability (ICC: 0.98–0.99) and moderate convergent validity (rho: 0.64–0.65).^37
38^

Tactile sensitivity will be assessed using the Semmes-Weinstein monofilament test, which measures cutaneous pressure detection thresholds through the application of calibrated nylon monofilaments applied perpendicularly to the skin surface. Testing will be conducted according to the Bell-Krokoski method,^44^ using a set of five monofilaments with diameters of 2.83, 3.61, 4.31, 4.56 and 6.65. Five anatomical sites will be tested on each upper limb: the pulp of the middle finger (D3; median nerve), the pulp of the little finger (D5; ulnar nerve), the first dorsal web space between the thumb and index finger (radial nerve), the lateral epicondyle over the extensor muscle compartment (lateral antebrachial cutaneous nerve) and the deltoid region (axillary nerve). Participants will be instructed to verbally indicate when the stimulus is perceived. The smallest monofilament detected at each site will be recorded, with lower scores indicating greater tactile sensitivity. The test has a moderate test–retest reliability (ICC: 0.46–0.61).^45^

*Proprioception:* The proprioception subtest of the Fugl-Meyer Assessment will assess the participant’s ability to locate their joint position in space at the shoulder, elbow, wrist and thumb. The evaluator performs four trials for each joint. The score ranges from 0 (absence) to 2 (correct 100%, little or no difference). For stroke survivors, there is an excellent inter-rater reliability (ICC: 0.93–1.0) and a good validity (r: 0.75),^46^ but this was not validated for SCI.

*Coordination:* The finger-to-nose test, performed based on the Comprehensive Coordination Scale,^47^ assesses smooth and coordinated upper limb movement. The participant is asked to alternately touch their nose and a target placed at arm’s length. The examiner scores four behavioural elements (trunk stability, arm movement, movement smoothness and endpoint accuracy) with a score ranging from 0 (impaired coordination) to 3 (normal) for each parameter. The time to complete five movement cycles is also recorded. The scores for each behavioural element are added for each side. The upper limb subscale of the Comprehensive Coordination Scale, developed for the stroke population, has excellent inter-rater reliability (ICC: 0.96) and intra-rater reliability (ICC: 0.96) and a moderate convergent validity (moderate–strong correlations with upper limb measures) in chronic stroke survivors.^47^

##### Neurophysiological assessment

Neurophysiological assessments will be conducted at T1, T2 and T3 by trained personnel with extensive experience in neurophysiological assessment to characterise neuroplastic changes in the central nervous system. TEPs induced by electrical stimulation will be used to assess changes in spinal neuronal networks. MEPs elicited by TMS will be used to assess corticospinal changes. For both methods, the responses to the stimulation will be recorded from the target muscles using electromyography (EMG). SEPs following median nerve stimulation will be recorded with EEG to assess sensory changes.

*Electromyography:* EMG activity will be recorded bilaterally from the following muscles, namely, biceps brachii, triceps brachii, extensor carpi radialis, flexor carpi radialis and first dorsal interosseous, using surface electrodes (Ag-AgCl, Blue sensor; interelectrode distance of 15–20 mm), secured to the skin over the belly of each muscle in accordance with SENIAM recommendations.^48^ EMG signals will be filtered (bandpass 10 Hz–1 kHz), amplified (500–1,000) and sampled at 2 kHz for online and offline analyses (CED Micro1401 with Signal software; Cambridge Electronic Design, UK).

###### Transspinal-evoked potentials

Single-pulse transcutaneous spinal stimulation is a non-invasive procedure used to assess the excitability of spinal pathways. Participants will remain comfortably seated in a chair or in their wheelchair. Self-adhesive surface electrodes will be placed over the cervical spine, with the cathode (Dura-Stick Plus double wire, Dura-Stick, US) positioned at the midline over C4-T1 and anodes over the external part of the clavicles (ROHVEMJ transcutaneous electrical nerve stimulation electrodes). Single-pulse tSCS will be delivered using a constant-current stimulator (DS8R, Digitimer, UK) with monophasic square-wave pulses of 1 ms at a frequency of 0.2 Hz to induce TEPs. Responses will be recorded from surface EMG. Stimulation intensity will be gradually increased to evoke a response in all, or the maximum possible number of, recorded upper limb muscles. The outcome measures will be: (i) motor threshold for each muscle, defined as the lowest intensity inducing 5 responses out of 10 stimulations; (ii) recruitment curve for each muscle and (iii) amplitude, latency and duration of the TEP at 120% of the motor threshold, determined for the myotome that showed the smallest response. Rest periods will be provided as needed to ensure participant comfort.

